### **8.7 Monitoring of the participants**

To minimize the risks during study participants are continuously monitored by trained medical personal. Physicians are available at the research institute during the complete duration of study. All personal involved in the study is specifically trained at begin of the study.

## **9. Adverse Events**

### **9.1 Definitions**

An **adverse event (AE)** is any untoward medical occurrence in clinical investigation subject and which does not necessarily have a causal relationship with this treatment.

It includes every untoward medical occurrence in a patient or clinical investigation subject administered a pharmaceutical product or in our case a food supplement between first intake and 24hours after the last administration.

An adverse event (AE) can therefore be any unfavorable and unintended sign (including an abnormal laboratory finding), symptom, or disease temporally associated with the use of a medicinal (investigational) product, whether or not related to the medicinal (investigational) product

Preexisting Diseases which worsen during the study are also defined as AE. AEs can become serious adverse events if they fulfill following criteria.

A **serious adverse event (SAE)** is defined as each adverse event or side effect that independently from causality occurs between first administration and 24hours after the last administration and fulfills following criteria:

- results in death (remark: death is the consequence and not the event)
- is life-threatening, (remark: the term “life- threatening” describes an situation in which a patient is in danger to life, and not an event which could lead to death if it would have been more serious)
- requires inpatient hospitalization or prolongation of existing hospitalization,
- results in persistent or significant disability/incapacity, or
- is a congenital anomaly/birth defect.
- Event which leads to an action to prevent one of the above mentioned criteria.

An **adverse drug reaction** is defined as any adverse event (as defined above) for which a causality with the study is possible, likely or certain.

A **serious adverse drug reaction** is defined as any severe adverse event (as defined above) for which a causality with the study is possible, likely or certain.

An **unexpected serious adverse drug reaction** is a severe adverse event that is not a typical adverse event for the test drug or intervention documented in the information sheet for trial participants.

## 9.2. Handling and documentation of adverse events

All serious adverse events occurring during the trial are documented in the CRF. The severity or intensity of the adverse event is rated with a 4-point scale (mild, medium, severe, life-threatening) and documented in the CRF.

- Mild: events, not influencing daily life
- Medium: disorders that curb or impair normal daily activity
- Severe: inability to work or execute normal daily activity
- life-threatening: direct danger to life

The connection between treatment and adverse event has to be assessed.

Etic commission is informed as fast as possible about all serious and unexpected serious adverse drug reaction (as defined in 9.1) occurring during the study.

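### Section 9.2 grades laboratory findings by daily activity, so a marked symptom-free liver-enzyme rise is recorded as mild, and the undated check-up in 6.7 may fall outside the 24-hour window in 9.1

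*Protocol*

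**What the plan says.** **Grading.** Protocol 9.2 uses four intensity grades. The lowest is "Mild: events, not influencing daily life" and the third is "Severe: inability to work or execute normal daily activity". The second grade, medium, is also defined by impairment of daily activity. Only the fourth, life-threatening, uses another criterion. No scale for laboratory values is given. The same section adds that "The connection between treatment and adverse event has to be assessed".

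**What counts.** Section 9.1 says that an adverse event can be "any unfavorable and unintended sign (including an abnormal laboratory finding", so laboratory abnormalities are covered. Section 8.3 cites case reports of liver-enzyme changes and finds a causal link with raised transaminases plausible in 7 of 216 reports. Section 7.3 lists adverse events as a secondary outcome.

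**Window.** For adverse events, 9.1 includes occurrences in a subject given "in our case a food supplement between first intake and 24hours after the last administration". A serious adverse event is one that "occurs between first administration and 24hours after the last administration and fulfills following criteria".

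**Checks after dosing.** Section 6.7 plans a check-up resembling the preliminary one, after the study day, with no day or hour. The preliminary check-up (6.1) measures GOT, GPT, γGT and bilirubin.

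**Terms.** Having defined *serious* adverse event, 9.1 says of a serious reaction to the drug that it "is defined as any severe adverse event (as defined above) for which a causality with the study is possible, likely or certain", and of an unexpected one that it "is a severe adverse event that is not a typical adverse event for the test drug or intervention". Section 4.5 also writes *severe* where it says when stopping the study would be discussed.

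**The concern.** A raised transaminase is usually found by a blood test, not by a complaint. A scale built on daily activity cannot separate a trivial rise from a large one if neither causes symptoms. The protocol brings such findings into its adverse-event definition and names them as a reported risk, then grades them by a criterion that does not respond to their size.

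The timing adds to this. If liver enzymes are first re-measured after the 24-hour window has closed, a rise could be left out of the adverse-event record, or a serious one could fail the serious-event definition.

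What is at stake is the accuracy of the safety record, which is a secondary outcome. The oral-clearance comparison is not affected.

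**Working it through.** The protocol gives no figure to reproduce. The check is a comparison of sections with one piece of clock arithmetic.

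**Step 1: which grade fits.** Take a marked GOT or GPT rise with no symptoms and no direct danger to life.

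| Grade in 9.2 | Criterion | Met? |
|---|---|---|
| Mild | No effect on daily life | Yes |
| Medium | Daily activity impaired | No |
| Severe | Unable to work or carry out daily activity | No |
| Life-threatening | Direct danger to life | No |

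Only mild fits, whatever the size of the rise.

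**Step 2: when liver enzymes are measured.**

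- Before dosing: at the preliminary check-up (6.1, 6.5).
- Study day: blood is taken for kinetics, RNA, protein and CRP (6.5). Liver enzymes are not listed.
- After dosing: the 6.7 check-up. That it includes liver enzymes is inferred from its likeness to the preliminary check-up.

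**Step 3: where the window ends.**

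- Last administration: the study-day morning capsule, hour 0 (6.3). The schema in 6.4 shows no evening capsule that day.
- End of the 9.1 window: hour 0 + 24 = hour 24.
- Last kinetic sample: hour 10 (6.5).
- Time left for a check-up inside the window: 24 − 10 = 14 h.

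The protocol gives no clock time for intake. If it is between 07:00 and 09:00 (assumed), the last sample is between 17:00 and 19:00, and the window closes between 07:00 and 09:00 the next morning. A check-up the same evening is inside it. One the next day is inside only if done before the previous day's intake hour, and any later one is outside.

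**Step 4: how firmly 9.1 imposes the limit.**

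- Serious adverse events: the 24 hours are part of the defining sentence, so the limit binds.
- Adverse events: the 24 hours stand in a sentence about what the term includes. The next paragraph asks only for a temporal association with use of the product and gives no hour limit. The limit can be read as binding, but need not be.

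Section 9.3 does not settle the matter, because it requires follow-up of adverse events and does not say whether a finding first seen later is one.

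**Step 5: severe and serious.** The serious-reaction definition points back to something defined above it. The only candidate there is the serious adverse event; the intensity grades come later, in 9.2. The unexpected-reaction definition has no back-reference, but the term it defines contains *serious*. In 4.5 the natural reading is also serious adverse event. All three are slips of wording.

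**The case against.** The strongest reply is that little depends on the grade. Causality must be assessed (9.2) and adverse events followed up (9.3) at every grade. Individual stopping (4.4) is the investigator's judgement, and ethics notification depends on seriousness and causality. A rise that calls for preventive action can still be a serious adverse event under the last criterion in 9.1. All of this stands, and it limits the point to the record. It does not make mild an informative grade for a large enzyme rise.

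A second reply is that the 24 hours do not close the adverse-event definition, and that a rise seen soon after 4 × 2 + 1 = 9 capsules would naturally be judged to have begun before hour 24. This largely stands for adverse events. For serious adverse events the limit is explicit, and dating the onset of a silent finding remains a matter of judgement.

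A third reply is that section 8.3 expects no adverse effects over five days. That bears on how often the gap would matter. The 7 of 216 are a share of reports, not a risk per user, so the documents give no rate from which to estimate a frequency.

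Three stronger readings are tempting, and the documents do not support them:

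- **That a rise found after 24 hours is certainly lost.** Section 6.7 fixes no time, and the adverse-event wording leaves room to count it.
- **That writing *severe* for *serious* changes which reactions go to the ethics committee.** The reference back in 9.1 can only mean the serious adverse event.
- **That 4.5 needs a laboratory stop trigger.** That section states that no stop criteria are defined and promises only a discussion. The grading fault does not show that a trigger is required.

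**Conclusion.** The concern holds as a minor point. As written, 9.2 records a marked symptom-free GOT or GPT rise short of danger to life as mild. This follows from the stated definitions and needs no assumption.

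The window point is weaker. It is firm for serious adverse events and only a possible reading for other adverse events. It also rests on two things: that the 6.7 check-up includes liver enzymes, which its likeness to the preliminary check-up suggests, and that it takes place more than 24 hours after the study-day capsule, which the protocol neither requires nor prevents.

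The mix of *severe* and *serious* is editorial. The consequence is a safety record that may understate a silent liver-enzyme rise or leave it out. Nothing here shows a loss of participant protection at the level of individual care, and the sample size is not affected.

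**What to change.** - **9.2:** grade laboratory findings by multiples of the upper limit of normal or of the participant's baseline. Keep the daily-activity definitions for symptoms.
- **9.1:** extend the adverse-event and serious-adverse-event window through the 6.7 check-up.
- **6.7:** state a latest day for the check-up, so that the extended window has an end.
- **9.1 and 4.5 (editorial):** replace *severe* with *serious* in the two reaction definitions and in the sentence on discussing a stop. No new stop trigger is needed.

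The cost is a wording amendment to four sections and one case report form field for the laboratory grade. No new test is needed if the 6.7 check-up repeats the preliminary liver tests. The downside is a few more events graded above mild and possibly an extra reportable event, because the window is longer. The primary analysis does not change.

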### **9.3 Handling and follow-up of adverse events.**

All adverse events especially in causality with the test drug have to be followed-up until all symptoms completely fade away, the basal level is reached or the condition is stabilized. If there is a distinct explanation for the AE, it has to be documented in CRF.

## **10. Data management**

### **10.1 Data collection, data analysis and data transfer**

All data collected und this study is under data protection. Personal data with the exception to day of birth, age and gender will not be released from test facility. Only pseudonymized data is transferred in form of CRFs and stored for analysis

Only the investigators at the test facility are authorized to assign the pseudonymization code with the personal data of the participant. Upon end of the trial study documents are archived according to the actual rules of data protection law.

Study data is documented in case report forms (CRFs). Following documents are available for the study:

- documentation of informed consent
- screening
- inclusion and exclusion criteria
- study protocol
- completion of study
- documentation of AE

DNA/RNA and blood samples are pseudonymized with a study code (EGCG\_Kin) and a number for the participant. Samples are stored as long as storage is possible and as long as a scientific use in the purpose of the study is possible. Samples are stored for such a long period of time because many targets (e.g. in Genome, Transcriptome, Proteome, Metabolome) will be analyzed for the project but analysis of this targets is time consuming and can last for many years. Participants are explicitly informed and have consented on the unlimited storage of samples at the University of Ulm and the transfer of plasma and urine samples to the university Göttingen. If a participant asks for the premature destruction of the samples after given consent, the participant should contact the clinical study investigator. Using an identification list the samples can be assigned to the participant and afterward be destroyed. The participants are explicitly informed about this fact in the participant information sheet. Samples are only used to study kinetics and the effects of EGCG.

### **10.2. Pseudonymization of the data and professional discretion**

Persons with access to the data are informed about privacy and confirm with a signature the information on professional discretion. A transfer of data to other persons is forbidden.

### **Financial Support:**

German cancer aid

